# The modulatory role of internet-supported mindfulness-based cognitive therapy on extracellular vesicles and psychological distress in people who have had cancer: a protocol for a two-armed randomized controlled study

**DOI:** 10.1186/s13063-022-06045-x

**Published:** 2022-02-05

**Keywords:** Cancer, Distress, Extracellular vesicles, Internet, Online, Mindfulness-based cognitive therapy, Mindfulness-based intervention, Randomized controlled trial

## Abstract

**Background:**

Mindfulness-based interventions (MBIs) have been used in oncology contexts as a promising tool with numerous benefits for various health-related and psychosocial outcomes. Despite the increasing popularity of MBIs, few randomized controlled trials (RCTs) have examined their effects upon biological parameters. Specifically, no previous study has examined the effects of MBIs on extracellular vesicles (EVs), which are potentially important markers of health, disease, and stress. Moreover, the lack of RCTs is even more limited within the context of technology-mediated MBIs and long-term effects.

**Methods:**

The current study protocol presents a two-arm, parallel, randomized controlled study investigating the effects of internet-supported mindfulness-based cognitive therapy (MBCT) compared with treatment as usual (TAU). Primary outcomes are psychological distress and EV cargo of distressed participants with previous breast, colorectal, or prostate cancer diagnoses. Secondary outcomes are self-reported psychosocial and health-related measures, and additional biological markers. Outcomes will be assessed at baseline, 4 weeks after baseline (mid-point of the intervention), 8 weeks after baseline (immediately post-intervention), 24 weeks after baseline (after booster sessions), and 52 weeks after baseline. Our goal is to recruit at least 111 participants who have been diagnosed with breast, prostate, or colorectal cancer (cancer stage I to III), are between 18 and 65 years old, and have had primary cancer treatments completed between 3 months and 5 years ago. Half of the participants will be randomized to the TAU group, and the other half will participate in an 8-week online MBCT intervention with weekly group sessions via videoconference. The intervention also includes asynchronous homework, an online retreat after the fifth week, and 4 monthly booster sessions after completion of the 8-week programme.

**Discussion:**

This study will allow characterizing the effects of internet-based MBCT on psychosocial and biological indicators in the context of cancer. The effects on circulating EVs will also be investigated, as a possible neurobiological pathway underlying mind-body intervention effects.

**Trial registration:**

ClinicalTrials.govNCT04727593 (date of registration: 27 January 2021; date of record verification: 6 October 2021).

**Supplementary Information:**

The online version contains supplementary material available at 10.1186/s13063-022-06045-x.

## Introduction

Cancer remains one of the leading causes of death and accounted for 19.3 million new cases and 9.9 million deaths worldwide in 2020 [1, 2]. By 2040, these numbers are expected to increase to 30.3 million new cases and 16.3 million deaths [2]. However, survival rates are also increasing due to major advances in cancer diagnosis, treatment, and follow-up, which means that cancer will increasingly impact the lives of many people. This creates a need to control disease progression and recovery pathways to optimize the well-being, quality of life, and daily functioning of people with cancer.

Distress is among the main factors that negatively affect the quality of life of cancer patients, regardless of the type of cancer or the stage of disease progression [3–6]. It is defined as an unpleasant affective experience that affects psychological (cognitive/behavioural/emotional), physical, social, and/or spiritual domains of functioning. As a result, the ability to cope with the illness experience is severely impaired [7, 8]. Distress involves various experiences (e.g. anxiety; depression; fear; rumination) that vary from person to person and over time [5, 7]. Importantly, this is a common experience in people with cancer from the time of diagnosis through disease remission and long-term survivorship [4]. Hence, distress management becomes crucial but encounters numerous barriers, including underestimation of psychosocial needs and the stigma of receiving psychosocial support. Accordingly, many sufferers do not acknowledge their distress or avoid seeking professional help [8, 9].

Mindfulness-based interventions (MBIs) have been investigated as a viable approach to managing cancer distress and have become increasingly popular over the last two decades [10, 11]. These interventions are derived from ancient Buddhist meditation practices. They focus on bringing attention to the present moment, in an intentional, open, non-reactive, and non-judgmental way [12]. They aim to cultivate an attitude of observation, patience, and acceptance toward negative stressful experiences, rumination, and anxiety, rather than an attitude of judgment and avoidance [13].

In the context of cancer, the commonly used MBIs are mindfulness-based stress reduction (MBSR), mindfulness-based cognitive therapy (MBCT), and mindfulness-based cancer recovery (MBCR) [14]. These MBIs may include a variety of formal mindfulness meditation practices, such as body scan, sitting, and walking meditation, as well as informal practices that promote the integration of mindfulness strategies into daily routines, such as observing body sensations and bringing awareness into routine activities [15]. These interventions have shown promising results on several health-related and psychosocial dimensions, including reductions in distress, depression, anxiety, and fatigue, and through improvements in quality of life, sleep quality, posttraumatic growth, and mindfulness (e.g. [16, 17]; see [10, 11, 18–20] for reviews). A recent meta-analysis of 29 randomized clinical trials found small to medium size effects of MBIs on psychological distress, depression, anxiety, fatigue, sleep disturbances, fear of cancer recurrence and pain, both after post-intervention and at follow-up [10].

MBIs are usually conducted in a face-to-face mode. However, this presents difficulties and challenges, as face-to-face activities are not accessible to all cancer patients and survivors. Barriers to in-person participation in MBIs include living long distances from the health care facility, limited transportation or time, greater burden of the disease and/or cancer treatment (including pain and fatigue), some degree of disability and full family and work schedules [21–24].

The limitations of conducting a face-to-face intervention can be overcome by the internet- or application-based psychological activities [25–29]. These approaches have several advantages, including easier management of the specific needs of cancer patients, survivors, and caregivers; easier integration of practices into personal daily routines; reduction of costs for both patients and institutions; and expansion of the accessibility of psychosocial interventions to more people [21, 22, 30–34]. The great relevance of digital technologies has been highlighted in the current COVID-19 pandemic [33], as they play a central role in bringing together health care professionals and patients [35]. This is particularly important in more vulnerable groups, such as cancer patients and survivors [36, 37]. Overall, digital health interventions now present a unique opportunity to consolidate and strengthen psychological interventions, improve the response of health care providers in terms of individual needs, and reduce financial and human resources constraints.

However, the benefits of implementing MBIs using Internet-based tools are unclear [25]. In the specific case of online MBIs, including both healthy and clinical groups, the literature shows positive effects on depression, anxiety, well-being, and mindfulness skills [38, 39]. In relation to cancer patients, several studies suggest that technology-mediated MBIs are feasible and beneficial in improving various psychosocial and health-related outcomes [14]. These include psychological distress, stress symptoms, fatigue, anxiety, depression, mood disturbances, sleep quality, quality of life, spirituality, mindfulness skills, fear of cancer recurrence, and rumination [21, 33, 40–51]. Moreover, greater improvements in anxiety, depression, and posttraumatic growth [14] were reported for online MBIs (compared to control conditions). However, there are other reports of lack of improvement in some of these outcomes, including perceived stress [48, 52], depression, anxiety, fatigue [44, 45, 53], posttraumatic growth [49], rumination [48], physical health-related quality of life [21, 42, 44], pain, spirituality, mindfulness skills [45, 48, 53], and sleep-related measures [45, 52]. Thus, the literature information on conducting MBIs with internet-based instruments in cancer care is inconclusive. This may be due to the use of different methods in the reported studies (e.g. type and characteristics of the intervention; mode of delivery; selected outcomes; timing of assessment), and the high variability of sociodemographic and clinical characteristics of the observed groups [14, 48, 52]. This also shows that systematic studies targeting Internet-based MBIs are needed to understand how this valuable tool can be used to benefit all, especially in times of pandemic.

To date, few randomized controlled trials (RCTs) have been published for online MBIs in cancer care [14] and only a small part of these assessed the stability and progression of improvements over time [42, 52, 54]. A subset of these studies showed improvements in psychological distress, anxiety, rumination, and quality of life after intervention [42, 52, 54], while other studies reported no gains in depression [52], fear of cancer recurrence, and physical-related quality of life [42]. This conflicting data may be justified by the use of different self-reported psychosocial and physical outcomes to monitor the effectiveness of online MBIs.

In this regard, beneficial online MBIs should also have a positive effect on biochemical markers, as has been demonstrated with face-to-face interventions [55–58], which could help to extend the benefits of the procedure beyond self-report, and monitor the extent of those benefits. Previously reported data support that face-to-face MBIs modulate immune function [59], contribute to increased telomerase activity [60], and preserve telomere length [61]. These interventions also appear to reduce pro-inflammatory gene expression and inflammatory signalling, as well as salivary cortisol levels [17]. Reductions in pro-inflammatory cytokines, such as interleukin-6 (IL-6), tumour necrosis factor-alpha (TNF-α), and interferon gamma (IFN-γ) [62, 63] along with increases in anti-inflammatory cytokines including IL-4, were also reported [62], supporting that MBIs may help balance immune system activity [55, 57]. In another example involving individuals with prostate cancer, a combination of MBSR with diet affected prostate-specific antigen (PSA) levels [64]. Many other biochemical markers would be of relevance to this topic, but there is not a set of biomarkers that have been selected as preferential for this kind of study [58].

Research work on intercellular communication and signalling through extracellular vesicles (EVs) and their contents (e.g. DNA; mRNAs; microRNAs; proteins; lipids) is rapidly increasing. EVs are cell messengers of health, disease, and stress that circulate through body fluids, and contain important information about the current state of an organism [65–69]. Thus, EVs are now considered a promising tool for signalling a wide variety of biological events.

In addition, EVs are already used in cancer screening, diagnosis, and progression, regardless of the organ from which the EVs originate [70, 71]. It has been shown that the secretion of EVs by malignant cells is higher than that of non-malignant ones and that their content also differs in terms of nucleic acid and proteins [72, 73]. Moreover, EVs of malignant cells can influence their neighbouring cells and establish and develop a tumour microenvironment that promotes cancer growth, invasion, and metastasis [70, 71]. Overall, cell-to-cell communication through these vesicles plays a role in the biochemical processes associated with cancer progression and metastasis [70–73], opening an opportunity of investigating biomarker candidates with clinical relevance and developing innovative therapeutic targets in cancer [70, 71, 73].

Specifically, central nervous system (CNS) EVs are viewed with great enthusiasm, because they contribute to better understanding of brain functioning, improve therapeutic management of neurodegenerative and neuropsychiatric clinical conditions [66, 67, 74–76], and may help clarify mind-body interactions that remain unclear despite major advances in science and technology. Moreover, EVs cross the blood-brain barrier, implying that circulating CNS-EVs may contain valuable information about how mind activities may impact the body.

As far as we know, no study has yet addressed the impact of psychological interventions such as MBIs on circulating EVs. It is not known whether they are altered by such interventions, which is not surprising given that EV research is in its infancy. There are also technical challenges involved in isolating CNS-derived EVs, from biofluids such as plasma [71, 73, 74, 76], which are currently being addressed by the project MindGAP (funded by the European Commission).

Therefore, the primary aim of this study is to observe the effect of an internet-based MBCT intervention (*vs*. treatment as usual) on CNS-EV cargo (objective measure) and psychological distress (subjective measure), in a sample of distressed people with a history of breast, prostate, and colorectal cancer.

A secondary objective is to monitor the direct impact of online MBCT on the overall immunological response (objective measure). For this purpose, several biochemical markers in the blood will be evaluated, including the inflammatory response of interleukins IL-1, IL-6, IL-8, IL-10, IFN-γ, and TNF, and C-reactive protein. Other biomarkers that are related to cancer recovery after disease termination are also evaluated, including telomerase activity, antigens related to cancer (cancer antigen—CA 15-3; prostate-specific antigen—PSA; carcinoembryonic antigen—CEA), and other health-related markers (adrenocorticotropic hormone; erythrocytes; glycosylated haemoglobin). While biomarkers of cancer recovery are routinely monitored in recovered patients, biomarkers of immunological response are intended to provide a more general picture of the impact of MBCT upon the overall immunological response. This is important to generate relevant data to support any scientific conclusion about the mind-body interaction.

Similarly, secondary subjective psychosocial parameters are also considered, namely quality of life, fear of cancer recurrence, emotion suppression, mindfulness abilities, sleep quality, posttraumatic growth, health-related behaviours (physical activity; nicotine dependence), and perceived social support. Care was taken to select brief measures, to minimize participant burden.

To evaluate these global objectives, a one-site two-arm parallel randomized controlled superiority study with a 1:1 allocation ratio to internet-supported MBCR vs. TAU will be conducted, with outcomes measured at five distinct time points: (1) baseline; (2) 4 weeks after baseline (mid-point of the intervention, some self-report measures only); (3) 8 weeks after baseline (post-intervention); (4) 24 weeks after baseline; and (5) 52 weeks after baseline. The last two time points will provide evidence for evaluating the long-term effects of online MBCT.

## Methods

The Standard Protocol Items: Recommendations for Intervention Trials (SPIRIT) 2013 checklist that supports this study can be consulted in Additional file 1.

### Study setting

The study is conducted at the Instituto Português de Oncologia do Porto (IPOP; Portuguese Oncology Institute of Porto), a reference hospital for cancer in northern Portugal. Data are being collected from Portuguese patients of this hospital. Public data about this trial can be obtained on the website of the project funding this study [77]. The majority of the interactions with participants are being conducted via internet-based platforms.

### Participants

#### Eligibility

The inclusion criteria are summarized in Table 1. It is noteworthy that breast, prostate, and colorectal cancer diseases were selected, as they are the most common cancers in Portugal, with both sexes included [78]. Completion of primary treatments was also considered to minimize the impact of cancer treatment on biological markers, also considering that psychological distress may still be present in people who have had cancer, regardless of survival stage (at least up to 5 years) [79].

**Table 1 Tab1:** Eligibility criteria

Inclusion	Exclusion
• Age between 18 and 65 years old* • Diagnosis of breast, prostate, or colorectal cancer (cancer stage I to III) • Primary cancer treatments completed between 3 months to 5 years previously (ongoing hormonal therapy will be included) • Experience of significant distress at the time of inclusion (DT ≥ 4) • Willingness to accept randomization to one of the two study conditions and participation in the intervention and data collection for the duration of the study • Ability to speak, read, and write in Portuguese and literacy to autonomously complete the self-report measure • Sufficient digital literacy and access to a device (e.g. smartphone; tablet; computer) with a camera, microphone, and internet	• Concurrent diagnosis of severe psychiatric condition(s) (e.g. bipolar disorder; psychosis; substance abuse; suicidal ideation) • Concurrent diagnosis of autoimmune disorder • Current use of antipsychotics • Current use of anti-inflammatory medication (e.g. corticotherapy) • Ongoing trastuzumab therapy • Participation in a structured mindfulness programme (e.g. MBCR; MBCT; MBSR) in the past 5 years • Currently attending psychological consultation • Being pregnant or breastfeeding

*Note*. *DT* distress thermometer, *MBCR* mindfulness-based cancer recovery, *MBCT* mindfulness-based cognitive therapy, *MBSR* mindfulness-based stress reduction. *This age criterion was considered due to other study of the MindGAP project in which healthy blood donors reporting low psychological distress will be compared with distressed participants diagnosed with cancer for a better characterization of the CNS-EVs. This characterization is important given that CNS-EVs are a novel approach in both healthy and clinical groups. As blood donors are aged between 18 and 65 years, the same criterion was applied to the participants diagnosed with cancer to have a closer age match between groups

In addition, participants must have significant distress at the time of inclusion, defined by a score of 4 or higher on the National Comprehensive Cancer Network (NCCN) Distress thermometer [8], as used in previous MBI studies [23], and considering that this cut-off score indicates moderate distress related to cancer [80, 81].

#### Recruitment

Two main strategies are planned to reach the target population. The first is based on obtaining a list of potential participants from the hospital’s Research Outcome Laboratory, filtered by relevant criteria, such as type of cancer and treatments. These potential participants will receive an informative email and/or SMS inviting them to visit the official website of the MindGAP project [77]. This website provides participants with more information about the study, including how to register. In the second variant, IPOP’s social networking sites (e.g. Facebook; Instagram; Institutional website) will be used to conduct regular dissemination and invite potential participants to visit the MindGAP’s website. Additionally, some health professionals working directly with the target groups will inform potential participants that the current study is recruiting and that more information can be obtained via the website.

In any case, participants can request more information by email or phone. Once contacted, participants receive a link to an online eligibility screening survey. This survey consists of an informed consent form and sociodemographic and health-related questions. If eligibility criteria are met, participants are invited to proceed in the study and to complete the baseline assessment. If any risk is identified (e.g. suicidal ideation), participants are informed about how to access specialist care services.

#### Informed consent

Informed consent is obtained directly from potential participants, via the online survey mentioned earlier. Specifically, participants are asked to confirm that they have read the information provided and are willing to collaborate, by checking a box. They will also be asked to authorize the research team to contact them regarding this study, access individual clinical records, and record the intervention sessions. Alternatively, participants will have the option to check a box to end their collaboration.

#### Sample size estimation

Because no previous study has examined circulating EVs in relation to MBIs and cancer, we could not use a specific effect size in estimating the sample size. Nonetheless, a recent systematic review examining the effects of Internet-based MBIs on psychological distress (anxiety and depression) found a median Cohen’s *d* value between 0.38 and 0.42 for the other primary outcome, psychological distress [14]. By using G*Power-3.1 statistical software [82] and considering repeated-measures ANOVA related to within-between interaction (group × time interaction), with an alpha significance level of 0.05 and an effect size of 0.38 (as calculated in [83]), a sample of 84 participants would allow for a power of 0.80. Additionally, previous studies showed dropout rates ranging from 12.1 to 32% for the intervention group and from 6 and 17.4% for the control group, when considering the period immediately following the intervention [23, 32, 40, 47, 49, 52, 84]. At follow-up, dropout rates were about 30.8% in the intervention group and 19.6% in the control group [52]. Considering the highest dropout rate (32%), 27 participants should be added to the estimated sample, resulting in a minimum of 111 participants to be included in the study.

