The timing of these measures is shown in Table 4. All psychosocial measures employed at baseline (T1) are used at T3, T4, and T5. In the fourth week after the baseline (the fourth session in the case of the intervention group), self-reported measures of distress and mindfulness will be used. This intermediate point (T2) was considered as previous studies have suggested that four sessions are the minimum satisfactory intervention dose [14, 52, 84, 89]. Few measures were selected at T2 to avoid participant burden. Regarding biological samples, the plans are to collect them at T1, T3, and T4. Of note, participants will receive financial compensation for the costs they incur traveling to IPOP to participate in the blood collections.

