### Assignment of intervention

#### Allocation

Participants will be randomly assigned to one of the two arms: MBCT or TAU groups (1:1 allocation ratio). Randomization blocks will be created using informatic tools and the entire process will be overseen by an investigator who will not be directly involved in the intervention or assessments. This investigator will inform the research team of the final allocation of each participant.

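### The stated 0.80 power at 84 participants is not supported for a Cohen's d of 0.38: no conversion to the ANOVA metric is shown, and 0.80 needs repeated-measures correlations of about 0.7 to 0.8 that the article does not state

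*Protocol article*

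**What the plan says.** All of the sizing is in the Sample size estimation section of the protocol article. No effect size was available for extracellular vesicles, so the trial is sized on psychological distress. A review is cited for a median Cohen's d "value between 0.38 and 0.42 for the other primary outcome, psychological distress". The test is a "repeated-measures ANOVA related to within-between interaction (group × time interaction"), run in G*Power 3.1 "with an alpha significance level of 0.05". The result is given as "an effect size of 0.38 (as calculated in [83]), a sample of 84 participants would allow for a power of 0.80".

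Three other places bear on this. Allocation is to "MBCT or TAU groups (1:1 allocation ratio"), so 84 analysed means 42 per arm. The Introduction describes a design "with outcomes measured at five distinct time points". Under Outcome measures, at the week-4 visit "self-reported measures of distress and mindfulness will be used", so distress is measured at all five. Statistical methods plans linear mixed models containing the group by time interaction. The Discussion concedes that the trial may be underpowered for extracellular vesicles and makes no such concession for distress.

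**The concern.** The value drawn from the review and the value used in the calculation are the same number, 0.38. The review's figure is a Cohen's d, the difference between means in SD units. The ANOVA procedure works in Cohen's f, which for two equal groups is d/2. An f of 0.38 therefore corresponds to a d of about 0.76, twice the cited effect. The article does not say which metric its effect size is in, and it shows no conversion.

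Distress is the only primary outcome that the trial could size. If the power for it is overstated, a null DASS-21 result may be read as evidence against an effect that the trial was quite likely to miss. Because the Discussion flags low power for vesicles alone, a reader will assume that distress is adequately covered.

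**Working it through.** **Inputs from the article:** d = 0.38; alpha 0.05; target power 0.80; two arms, 1:1; N = 84 before dropout; five time points for distress.

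**Assumptions, not in the article:** 0.38 is a between-arm difference; a common correlation ρ between repeated measures (compound symmetry); 84 analysed.

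**1. Reproducing 84.** Take 0.38 as f, with noncentrality λ = f²N and df = m−1 and (N−2)(m−1) for m measurements. The first even N with power of at least 0.80 is:

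- m = 2: 58
- m = 3: 70
- m = 4: 78
- m = 5: 84

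At m = 5 and N = 84, λ = 0.1444 × 84 = 12.13 and power is 0.801. N = 82 gives 0.790. The match is exact, and it occurs at the trial's own number of time points.

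**2. Other routes to 84.** With f = 0.19 and λ = f²Nm/(1−ρ), m = 2 and ρ = 0.25 gives λ = 0.0361 × 84 × 2/0.75 = 8.09 and N = 84; m = 3 and ρ = 0.1 gives N = 82. At m = 5, f = 0.38 with λ = f²N is algebraically the same as f = 0.19 with λ = f²N(m−1), since 0.1444 = 4 × 0.0361. So 84 alone does not identify how it was obtained.

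**3. Power for d = 0.38 at one time point.** Noncentral t, 42 per arm, two-sided 5%: noncentrality 0.38 × √(42/2) = 1.74, power 0.41. For the upper cited d of 0.42 it is 0.48. With baseline adjustment the effect becomes 0.38/√(1−ρ²), and power is 0.51 at ρ = 0.5 and 0.67 at ρ = 0.7.

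As a check on the two-measurement route in step 2: a change-score comparison at ρ = 0.25 has standardised effect 0.38/√(2 × 0.75) = 0.31 and power of about 0.29, not 0.80. Halving d overstates the interaction f when the arms differ only after baseline.

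**4. Power for the planned five-point interaction.** Under compound symmetry λ = (N/4) × S/(1−ρ), where S is the sum of squared deviations of the between-arm differences from their mean over the five visits. Here N/4 = 21, with 4 and 328 df.

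- Effect sustained from T2 (differences 0, d, d, d, d): S = 0.1444 × 4/5 = 0.1155.
- Effect starting at T3 (0, 0, d, d, d): S = 0.1444 × 6/5 = 0.1733.

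| Assumed ρ | Sustained from T2 | Starting at T3 |
|---|---|---|
| 0 | 0.20 | 0.29 |
| 0.5 | 0.38 | 0.55 |
| 0.7 | 0.60 | 0.80 |
| 0.8 | 0.80 | 0.94 |

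The λ of 12.13 needed for 0.80 is reached when 21 × 0.1155/(1−ρ) = 12.13, that is ρ = 0.8, or when 21 × 0.1733/(1−ρ) = 12.13, that is ρ = 0.7.

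**5. Detectable effect at 84 analysed, power 0.80, single-time-point contrast:** d = 0.62 unadjusted; 0.54 and 0.44 with baseline adjustment at ρ = 0.5 and 0.7.

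**The case against.** The strongest reply has four parts.

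- **The mechanism is inferred.** A reader might conclude that 84 can arise only from entering d as f. The documents do not support that. The G*Power option, number of measurements and correlation are not reported, the source cited for the effect size is not shown, and step 2 gives routes to 84 with the correctly halved f. This stands, so the swap is offered as the best-fitting explanation only.
- **There is no single true power.** A reader might also take 0.4 to 0.7 as the trial's actual power. That range depends on correlations of about 0.5 to 0.7 that appear nowhere in the article, and on when the effect begins. Across the two sustained patterns in step 4, power runs from 0.20 to 0.94. This also stands.
- **A single-time-point contrast is not the planned test.** The article sizes and plans a group by time interaction and names no visit as primary. The 0.41 is therefore a reference value; the table in step 4 is the relevant one.
- **Another analysis could do better.** A baseline-adjusted average over three or four follow-ups has power 0.77 or 0.81 at ρ = 0.5, and 0.88 or 0.90 at ρ = 0.7. That is correct, but it is not the interaction test on which the figure of 84 rests.

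A journal article may leave software settings to the full protocol. The point here is not the missing detail. A stated power does not follow from the stated effect unless high correlations are assumed.

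**Conclusion.** The claim of 0.80 power for distress is not supported as written. With 0.38 read as a between-arm d and 84 analysed, the planned five-point test reaches 0.80 only at correlations of about 0.7 (effect starting at T3) to 0.8 (sustained from T2) or higher. At a correlation of 0.5 it has 0.38 to 0.55. Step 3 shows that the two-measurement route to 84 does not restore 0.80 either.

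The exact match with f = 0.38 over five measurements makes a d-for-f substitution likely but unproven. The conclusion on power does not depend on it. It rests on three assumptions: 0.38 is a difference between arms, compound symmetry holds, and the effect follows one of the two patterns examined.

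**What to change.** Redo the calculation for the planned DASS-21 group by time contrast with d converted correctly. State the effect-size metric, the number of measurements, the assumed correlation and the G*Power option.

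If N is not to change, replace the 0.80 claim by one of these:

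- the power at d = 0.38 over a stated range of correlations, as in step 4; or
- the detectable effect at 84 analysed, labelled as a single-time-point contrast: d about 0.62 unadjusted, or 0.54 and 0.44 baseline-adjusted at correlations of 0.5 and 0.7.

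In the Discussion, extend the low-power limitation from extracellular vesicles to distress.

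The cost of keeping N is a reworded sample size paragraph and one added limitation. The stated figure becomes less favourable; no extra participants are needed.

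### The dropout allowance adds 32% of 84 instead of dividing 84 by 0.68, so 111 recruits leave about 75 completers at the stated dropout rate, not the 84 required

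*Protocol article*

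**What the plan says.** The Sample size estimation section takes its effect size from a systematic review of internet-based mindfulness interventions. It sizes the trial on the group-by-time interaction in a repeated-measures ANOVA, "with an alpha significance level of 0.05 and an effect size of 0.38", and concludes that "a sample of 84 participants would allow for a power of 0.80".

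It then reports attrition in earlier studies for the period just after the intervention: "dropout rates ranging from 12.1 to 32% for the intervention group and from 6 and 17.4% for the control group". For follow-up it gives about 30.8% (intervention) and 19.6% (control).

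From these it takes the single highest figure and applies it to the whole sample: "Considering the highest dropout rate (32%), 27 participants should be added to the estimated sample, resulting in a minimum of 111 participants". The Methods part of the abstract repeats the result as the recruitment target: "Our goal is to recruit at least 111 participants".

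**The concern.** The allowance exists so that enough participants remain after dropout to keep the power computed for 84. The percentage has been taken of the wrong base. The dropout rates quoted from earlier studies are shares of those who entered a study group, whereas the article takes 32% of the number it wants to have left. The two operations diverge as the rate rises, and at 32% the gap is too large to be rounding.

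At stake is the stated power. If 111 does not deliver 84 at 32% dropout, the article's figures for sample size, dropout and power cannot all be true together. There is little slack elsewhere. The Discussion concedes that the trial may be underpowered for the extracellular vesicle outcome and that poor adherence and retention could make this worse. The Statistical methods section also discards data from MBCT participants who complete fewer than four sessions, which could reduce the analysed number further.

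**Working it through.** **Inputs (Sample size estimation section unless stated)**
- Required sample before dropout: 84, for power 0.80 at alpha 0.05
- Dropout rate used: 32%, one rate for everyone
- Arm-specific rates quoted but not used: intervention 12.1–32%, control 6–17.4% after the intervention; 30.8% and 19.6% at follow-up
- Allocation 1:1 (Allocation section), so 55.5 per arm on average with 111

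**Step 1. Reproduce the article's figure.**
84 × 0.32 = 26.88, rounded to 27. Then 84 + 27 = 111, equivalently 84 × 1.32 = 110.88. Both stated numbers are reproduced exactly, so the method used was N × (1 + d).

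**Step 2. What 111 delivers at 32%.**
111 × (1 − 0.32) = 75.48, about 75 completers. Against 84 this is 8 to 9 short.

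**Step 3. What is needed at 32%.**
N / (1 − d) = 84 / 0.68 = 123.5, so 124 (62 per arm). Check: 124 × 0.68 = 84.3. That means adding 40 rather than 27, and 124 − 111 = 13 more recruits.

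**Step 4. The dropout that 111 can absorb.**
1 − 84/111 = 0.243. The target keeps 84 completers only if overall dropout is at most 24.3%.

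**Step 5. Effect on power.**
The article does not give every input of its power calculation, so I took its claim of power 0.80 at 84 as correct and scaled from there. The test is an F test with m − 1 and (N − 2)(m − 1) degrees of freedom for m measurements. Its noncentrality is c × N, with c set so that N = 84 gives 0.80.

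| Measurements m | c | Power at 75 | Power at 82.4 | Power at 83.5 |
|---|---|---|---|---|
| 2 | 0.0957 | 0.753 | 0.792 | 0.798 |
| 3 | 0.1168 | 0.750 | 0.792 | 0.797 |
| 4 | 0.1319 | 0.748 | 0.791 | 0.797 |
| 5 | 0.1442 | 0.746 | 0.791 | 0.797 |

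Power at 75 completers is therefore about 0.75, whatever the number of measurements assumed.

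**Step 6. Sensitivity: arm-specific rates.**

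| Intervention / control dropout | Completers from 111 | Total to recruit for 42 completers per arm |
|---|---|---|
| 32% / 17.4% | 55.5 × 0.68 + 55.5 × 0.826 = 37.74 + 45.84 = 83.6 | 62 + 51 = 113 |
| 30.8% / 19.6% | 38.41 + 44.62 = 83.0 | 61 + 53 = 114 |
| 32% / 19.6% | 37.74 + 44.62 = 82.4 | 62 + 53 = 115 |

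Unequal arms cost a little more. For the first pair the equivalent balanced sample is 4 × 37.74 × 45.84 / 83.58 = 82.8, which lies between the last two columns of the power table. Power is then roughly 0.79 to 0.80.

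**The case against.** The strongest reply is that 32% in both arms is harsher than anything the article cites. That figure is the top of the intervention-arm range, and every control-arm rate quoted is below 20%. With the worst post-intervention rate in each arm, the average loss is (32 + 17.4)/2 = 24.7%, barely above the 24.3% that 111 can absorb, and the shortfall is less than one completer. This stands as a statement about likely practical impact. It does not rescue the text, which applies one rate of 32% to the whole sample and gives no arm-specific reasoning. Even on the arm-specific pairs in the sensitivity table, 111 falls slightly short of 84.

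Three further points have some weight:
- **Partial data.** The planned analysis is a linear mixed model, which can use the visits of people who leave later. Counting each dropout as wholly lost is therefore pessimistic. But the sample was sized on a repeated-measures ANOVA with an add-on for dropout, and the article does not offer partial data as its reason for 111.
- **111 is a minimum.** More may be recruited. But a stated minimum should be sufficient under its own assumption, and this one is not.
- **The four-session exclusion.** Those who attend fewer than four sessions may largely be the same people already counted as dropouts. The overlap is unknown, so I attach no number to this rule.

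**Conclusion.** The concern holds. The inflation step uses 84 × 1.32 = 111 where a 32% loss calls for 84/0.68 = 124. At the article's own rate, its minimum leaves about 75 completers and power of about 0.75 rather than 0.80.

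The size is moderate: about 5 percentage points of power at 32% in both arms, and about 1 point or less with the arm-specific rates that the article quotes. The counts follow from the article's figures alone. The power values rest on two assumptions: that 84 does give 0.80, and that a dropout contributes nothing to the analysis. The base figure of 84 is not challenged here.

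**What to change.** Correct the dropout sentence in the Sample size estimation section in one of three ways:

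- **(a)** Keep 111 and state what it delivers: about 75 completers at 32% dropout, with power of about 0.75.
- **(b)** Keep 111 and base it openly on arm-specific dropout of 32% (MBCT) and 17.4% (TAU), giving about 83 completers and power of roughly 0.79 to 0.80.
- **(c)** Keep the single 32% rate and state 124 as the minimum.

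Options (a) and (b) cost one sentence and a slightly less favourable stated power, with no extra recruits. Option (c) costs 13 more participants and also changes the target in the abstract. Whichever is chosen, the number and its justification should agree wherever the target is repeated.
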